**Fig. 1 Fig1:**
[figure not shown]
Flow of participants through the study

Following enrolment, treatment (either nonoperative or operative management) will be decided using a shared decision approach as mentioned above. Data will be acquired at 7, 14, and 30 days, and at 3 and 6 months after trauma.

Baseline data will be collected from the patient’s medical files or by interviewing the patient as soon as possible, but no later than at the visit after enrolment. At each follow-up visit, the coordinating researcher or research assistant will visit the patient. He will ascertain patient status (i.e., treatment details including analgesics and other health care use, mobility of the patients, adverse events/complications, secondary interventions, and will verify information within medical records). At each visit patients (or proxy) will be asked to complete a questionnaire for the EQ-5D. At those visits, a caregiver will be asked to complete the QUALIDEM and PACSLAC-D.

At the final visit at 6 months, patients (or proxy) and caregiver will be asked to complete a questionnaire relating to their satisfaction with the treatment approach. In case a patient has died during follow-up, his/her relatives and caregiver will be asked to complete this questionnaire. In addition, relatives will be invited for an interview to complete the QODD questionnaire. An early withdrawal form will be completed if patients (or proxy) decide to withdraw from the study.

### Blinding

As with many surgical studies, patients and surgeons cannot be blinded for the intervention. In order to reduce bias as much as possible, outcome assessment will be performed using a standardized protocol. Outcome measures include both objective and subjective items.

### Statistical analysis

Data will be analyzed using the Statistical Package for the Social Sciences (SPSS) version 24.0 or higher (SPSS, Chicago, Ill., USA) and will be reported following the STrengthening the Reporting of OBservational studies in Epidemiology (STROBE) guidelines. Normality of continuous data will be tested with the Shapiro-Wilk test. Homogeneity of variances will be tested using the Levene’s test. A two-sided *p*-value < 0.05 will be taken as threshold of statistical significance in all statistical tests. The analysis will be performed on a per-protocol basis, (as that is the most conservative approach) and verified by an intention-to-treat analysis if needed. Patients who have died will remain in the analysis as censored. If necessary, missing values will be replaced using multiple imputation following the predictive mean matching method, using ten imputations.

Descriptive analysis will be performed in order to report the outcome measures and other variables collected for the entire population as well as per treatment group. Continuous data will be reported as mean and SD (if Normal) or median and quartiles (if non-Normal), categorical data as number with percentage.

Univariate comparison between the groups will be done using Student’s T or Mann-Whitney U-test (for Normal and non-Normal data, respectively), or Chi-squared test or Fisher’s Exact test (categorical data, as applicable). The Student’s T-test will be done with equal variance assumed or not assumed, based upon the results of the Levene’s test.

For the primary outcome measure, a non-inferiority margin of 0.15 points for mean EQ-5D scores was chosen because it is reasonable and on the border of what would be considered a clinically important effect. The null hypothesis in the non-inferiority framework is that nonoperative management is inferior to operative management with regards to the EQ-5D score. This hypothesis will be tested through the adjusted contrast between the two interventions at 6 months. Specifically, the 95% confidence interval of the estimated contrast will be examined, and if the limit of the interval is less than the threshold value of 0.15 points, non-inferiority of nonoperative management to operative management at 6 months will be concluded.

Multivariable analysis for continuous outcome measures that are repeatedly measured over time will be done using generalized estimating equations (GEE) for longitudinal analysis on a per-protocol and intention-to-treat basis to investigate the effect of treatment. In the primary GEE model, the primary outcome variable studied (quality of life on EQ-5D) will be analyzed as a dependent variable, using treatment (nonoperative versus operative) as between subjects variable and time as within subjects variable. The interaction term of group and time (group x time) will be assessed, to evaluate whether the change over time differed between groups. Analyses will be corrected for baseline differences and all models will be corrected for center of inclusion. Repeatedly measured continuous secondary outcome variables will be analyzed using similar GEE models. Continuous outcome measures only ones and dichotomous secondary outcome measures will be analyzed using multivariable linear regression models and logistic regression models, respectively.

Subgroup analysis are planned for patients with an intracapsular or extracapsular fracture.

The economic evaluations will be done from a societal perspective. Intervention costs and health care utilization costs until 6 months after inclusion will be measured in accordance with economic guidelines [45]. Cost prices of the standardized referral strategy will be determined by bottom-up micro-costing method. The economic evaluation will be performed in accordance with the intention-to-treat principle. Missing data will be imputed using multiple imputation by changed equations [46]. The Incremental Cost-Effectiveness Ratio (ICER) of nonoperative versus operative management will be calculated by dividing the difference in costs by difference in effects. A cost-utility analysis, with QALY (based on the EQ-5D utility score) as outcome measure, will be done as primary economic analysis. As secondary analysis, a cost-effectiveness analysis, with QUALIDEM as outcome measure, will be done. In order to account for the possible clustering of data, analyses will be performed using linear multilevel analyses [47]. Accounting for the possible clustering of data (e.g., at the hospital level) is very important, as most economic evaluations fail to do so, whereas ignoring the possible clustering of data might lead to inaccurate levels of uncertainty and inaccurate point estimates [47]. Bootstrapping techniques will be used in order to estimate the uncertainty surrounding the cost-effectiveness estimates. Uncertainty will be shown in cost-effectiveness planes and cost-effectiveness acceptability curves, and sensitivity analyses will be performed in order to test the robustness of the study results [48–50].

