### Study design and setting

This study will be a two-arm non-randomized (observational) multicenter cohort study and an economic evaluation alongside. The study will be conducted with a non-inferior design. Relevant societies for surgery (Dutch Association of Surgery (NVvH), Dutch Association of Trauma Surgery (NVT), Dutch Orthopaedic Association (NOV), and Dutch Association of Orthopaedic Surgery (NVOT)), clinical geriatrics (Dutch Association of Clinical Geriatrics (NVKG)), elderly care (Association of Elderly Care Physicians (VERENSO)), the Dutch Patient Federation, and two committee members of the Dutch guideline for treatment of proximal femoral fractures are represented in the study team. Patients will be recruited from several hospitals throughout The Netherlands. The following 26 hospitals will participate: Albert Schweitzer Ziekenhuis, Alrijne Ziekenhuis, Amphia Ziekenhuis, Amsterdam UMC (location VUmc), Bernhoven, Catharina Ziekenhuis, Deventer Ziekenhuis, Dijklander Ziekenhuis (location Westfriesgasthuis), Dijklander Ziekenhuis (location Waterland Ziekenhuis), Elisabeth TweeSteden Ziekenhuis, Erasmus MC, Flevo Ziekenhuis, Isala, Maasstad Ziekenhuis, Meander MC, Noordwest Ziekenhuisgroep, OLVG, Radboud UMC, Rijnstate, Rode Kruis Ziekenhuis, St. Antonius Ziekenhuis, Streekziekenhuis Koningin Beatrix, Tergooi, Ziekenhuis Gelderse Vallei, Ziekenhuis Tjongerschans, and Zorggroep Twente.

The study has started in September 2018. The recruitment period will be 24 months, with a follow-up of 6 months. The results of the study are expected mid-2021.

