### Treatment of participants

#### Shared decision process

The decision for type of treatment (operative or nonoperative) is achieved by shared decision making (SDM). Shared decision making is based on determining the goals of care for the patient [27]. The purpose of goals of care is to safeguard patients who are unlikely to benefit from operative treatment, especially in patients in the palliative or terminal phase. Goals of care discussion with these frail elderly patients, or in case of cognitive impairment, with a proxy at the onset of proximal femoral fracture are useful in shared decision making. Although some form of SDM is also used in current practice, this study will use a much more structured approach towards this process. Prior to start of treatment, patients will be informed in an objective and structured way about what either treatment arm of the study involves and what complications may occur in either treatment arm. Both for nonoperative and operative management, a full forecast is given verbally and on paper. Combined with the preferences and objections of the patients or their proxy, this is the starting point of a shared decision process. All principal health care providers (i.e., a trauma or orthopedic surgeon, elderly care physician, and geriatrician if possible) as well as the patient and his/her relative(s) or legal representative will take part in this shared decision process. The patients perspective will play a key role in the decision process.

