#### Operative management group

Patient opting for operative treatment, will have operative management of the proximal femoral fracture (if no medical contra-indications or objections by treating physician). The choice of implant will depend on the fracture type, and will adhere to the Dutch guideline for hip fracture treatment [2]. In general, intracapsular femoral neck fractures will be fixed with a (hemi)arthroplasty or screw fixation, and extracapsular pertrochanteric fractures with a dynamic hip screw, dynamic compression screw, or an intra-medullary fixation. Perioperative care will be according to local hospital protocols in order to have a real-life situation. As soon as reasonably possible after surgery, patients will return to their nursing home for further (palliative) care. The principles for palliative care are the same as described for the nonoperative group. Relevant details of treatment will be registered for possible use in the statistical analysis.

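### Per-protocol is called the most conservative basis and intention-to-treat left conditional, although the GEE paragraph plans both; the non-inferiority rule names neither population

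*Protocol article*

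**What the plan says.** Four places in the protocol article bear on this.

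- **Statistical analysis, opening paragraph:** "The analysis will be performed on a per-protocol basis, (as that is the most conservative approach) and verified by an intention-to-treat analysis if needed". Nothing says what would make the second analysis necessary.
- **Statistical analysis, GEE paragraph:** repeated continuous outcomes, including the primary EQ-5D model, are analysed "for longitudinal analysis on a per-protocol and intention-to-treat basis to investigate the effect of treatment". No condition is attached.
- **Statistical analysis, primary-outcome paragraph:** non-inferiority is concluded if the limit of the 95% confidence interval for the adjusted 6-month contrast falls within 0.15. One interval is meant, and no population is named.
- **Statistical analysis, economic paragraph:** "The economic evaluation will be performed in accordance with the intention-to-treat principle".

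On design, Study design and setting states: "This study will be a two-arm non-randomized (observational) multicenter cohort study and an economic evaluation alongside". Under Shared decision process, "The decision for type of treatment (operative or nonoperative) is achieved by shared decision making (SDM"). The Operative management group section makes surgery conditional ("if no medical contra-indications or objections by treating physician"), and Study procedures and follow-up has secondary interventions recorded at the visits.

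**The concern.** Two things are wrong on the face of the text.

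First, the section takes two positions on whether intention-to-treat is run for the primary outcome: conditional in one paragraph, unconditional in another. The decision rule does not settle which result counts. Patients and surgeons are not blinded, so an analysis run only at discretion, with no rule for disagreement, leaves a choice that could be made after the results are known.

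Second, the reason given for preferring per-protocol does not carry over to this design. In a randomised non-inferiority trial the usual argument is that keeping crossovers in their allocated arm pulls the arms together and so helps a claim of non-inferiority. That argument does not cover who is lost when patients are left out. Here the arm follows from a shared decision, and patients who depart from that decision probably differ in prognosis from those who do not. Excluding or reclassifying them can therefore select on outcome, in either direction.

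At stake is the conclusion on the primary outcome, which the Discussion section says may feed into treatment guidelines.

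**Working it through.** **The plan's own figure.** The article gives no switching rate, no EQ-5D value for switchers and no figure for the effect of the population choice, so there is nothing to reproduce on this point. What follows illustrates direction and size only.

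**Inputs from the article.** Sample size calculation: SD 0.30, margin 0.15, 50 evaluable patients per arm. Statistical analysis: 95% confidence interval rule, so one-sided error 2.5% at the margin. The 50 per arm is taken as stated and serves only to set the standard error.

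**Assumed inputs.** A share c of one arm departs from the agreed treatment and is excluded. These patients score D lower on EQ-5D than the rest of their arm. Ranges: c = 5%, 10%, 20%; D = 0.1 to 0.3.

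**Shift in the mean.** If the remaining patients have mean m, the full-arm mean is m − c × D. Exclusion therefore raises the arm's mean by c × D.

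- c = 10%, D = 0.30: 0.10 × 0.30 = 0.03, and 0.03 / 0.15 = 20% of the margin.
- c = 20%, D = 0.30: 0.20 × 0.30 = 0.06, and 0.06 / 0.15 = 40% of the margin.

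**Error rate.** Let the true difference by agreed treatment (nonoperative minus operative) be −0.15, so that a claim of non-inferiority is an error. With n1 and n2 patients left in the arms, SE = 0.30 × √(1/n1 + 1/n2), and the one-sided error is Φ(shift / SE − 1.96).

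Worked case, 10% removed from the nonoperative arm, D = 0.30: n1 = 45, n2 = 50, SE = 0.30 × √(1/45 + 1/50) = 0.0616; 0.03 / 0.0616 − 1.96 = −1.47; error 7.0%.

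| Who is removed | Shift towards nonoperative, D = 0.1 to 0.3 | One-sided error |
|---|---|---|
| Nobody | 0 | 2.5% |
| 5% of nonoperative arm | 0.005 to 0.015 | 3.0% to 4.3% |
| 10% of nonoperative arm | 0.010 to 0.030 | 3.6% to 7.0% |
| 20% of nonoperative arm | 0.020 to 0.060 | 5.0% to 15.5% |
| 10% of both arms | 0 | 2.5% |
| 10% of operative arm only | −0.010 to −0.030 | 1.7% to 0.7% |

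With fewer evaluable patients the pattern is the same. If 60% of the 160 recruited are lost, 160 × 0.4 / 2 = 32 per arm remain, and the nonoperative-only rows run from 2.9% to 11.4%.

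**Opposite sign.** If the nonoperative patients who later have surgery do better than the rest (D negative), excluding them lowers the nonoperative mean and per-protocol becomes the stricter analysis. The direction thus depends on which arm loses patients and how they fare, and the article fixes neither.

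**The case against.** The strongest reply is that both analyses are already planned for the primary outcome. The adjusted contrast is a model result, and the GEE paragraph runs that model on both bases. This stands: intention-to-treat is not absent. What remains is the conflict with the opening paragraph and the missing rule for discordant results.

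A reader might go further and infer that the primary analysis does remove nonoperative failures and so favours nonoperative care. The article does not support that. It does not define the per-protocol set or say whether switchers are excluded or reclassified, and a journal article may leave that definition to the full protocol. The clause on contra-indications to surgery may describe what is weighed at the decision itself, not a later crossover. Late surgery could also restore quality of life, in which case per-protocol is the stricter analysis.

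A reader might also infer immortal-time bias, because operative patients must survive to surgery. For the primary outcome this hardly matters: someone who dies before surgery has no 6-month EQ-5D under either analysis.

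Nor does the economic evaluation necessarily rest on different patients from the clinical one, since an intention-to-treat clinical GEE is planned too.

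Finally, intention-to-treat here can only mean analysis by the treatment agreed. It leaves the selection bias that the Discussion section acknowledges, and making it the sole primary analysis would be a debatable preference.

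**Conclusion.** The point holds in limited form. The Statistical analysis section contradicts itself on whether intention-to-treat is conditional, its decision rule names no population and does not provide for disagreement, and its reason for preferring per-protocol is not assured in a non-randomised cohort. Bias from per-protocol exclusion is possible but not shown, and its direction is open.

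Under the assumed inputs, one-sided error moves from 2.5% up to between 3.0% and 15.5% when poor-outcome patients are lost only from the nonoperative arm (5% to 20% excluded), and down to between 0.7% and 1.7% when 10% are lost only from the operative arm. These figures rest on a normal approximation, SD 0.30, 50 per arm, and switching rates and EQ-5D deficits that the article does not give. They also set confounding aside.

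**What to change.** In the Statistical analysis section:

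1. Delete the condition on intention-to-treat and the claim that per-protocol is the most conservative approach.
2. For the primary outcome, make the analysis by the treatment agreed in the shared decision mandatory beside per-protocol.
3. State in the decision rule that non-inferiority is concluded only if the 95% confidence interval meets the 0.15 margin in both analyses. In the illustration above, this holds the error at or below 2.5% whichever arm loses patients, because the analysis by agreed treatment must pass as well.
4. Align the opening and GEE paragraphs with this rule.

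The cost is wording, since both analyses are already foreseen. The downside is that the claim must hold twice, which cannot raise power and may lower it. Neither analysis removes confounding by indication, so the planned adjustment for baseline differences is still needed.

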## Background

Proximal femoral fractures are amongst the most common fractures in the elderly [1] with the incidence rate increasing with age. In the Netherlands 20,000 patients are admitted with a proximal femoral fracture to the hospital each year [2, 3]. This number is expected to rise because of our ageing society. Approximately 20% live in a nursing home prior to the fracture. Proximal femoral fractures result in activities of daily living (ADL) dependence and increased morbidity, strongly diminishes the patients’ (health-related) Quality of Life (QoL) and total health care costs [4–7].

A proximal femoral fracture is also strongly associated with mortality. Over 30% of patients die within the first year and 8–13.3% die within the first month [8–10]. Mortality is highest among elderly with both physical and cognitive comorbidities [9, 10]. A 36 and 55% mortality rate within 6 months after fracture has been reported for institutionalized patients and patients with advanced dementia, respectively [11, 12]. This shows that the hip fracture is merely a symptom of the frail status of these patients and the start of cascade breakdown at the end of life.

Operative treatment allows early mobilization, is effective in pain relief, and is believed to prevent secondary complications like pneumonia, urinary tract infection, and pressure sores. However, surgery will not prevent frail patients from developing aforementioned complications. Instead, patients may develop additional surgical complications like bleeding, infection, and non-union, necessitating further (operative) interventions [13]. Hospital admission after a proximal femoral fracture itself can provoke cognitive impairment or delirium in these patients who often live in delicate equipoise in an institutionalized setting.

Although surgery is considered a good analgesic option, it is not the only analgesic option. Moreover, surgery also has disadvantages. It is questionable whether surgery is beneficial in terms of quality of life and whether surgery is satisfactory for family and caretakers involved. The World Health Organization (WHO) definition for palliative care supports a holistic approach in facing life-threatening illness, which is a proximal femoral fracture in a frail elderly patient. Randomized trials comparing operative and nonoperative management in institutionalized elderly are scarce, due to ethical issues, and focus on mortality instead of quality of life.

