Guidelines have no strict advice for frail elderly with a proximal femoral fracture, as a result of lack of evidence on palliative care in these patients. The National Institute for Health and Care Excellence (NICE) advises to discuss if patients are open to hospital admission and possible surgery [14]. Dutch guidelines advocate operative treatment in patients with a life expectancy beyond 6 weeks [2, 15]. This leads to practice variation. Current practice is that over 90% of femoral fracture patients that presented to hospital are operated, even if they are institutionalized and have a limited life expectancy [16].

A systematic review of the literature on nonoperative management versus operative management of proximal femoral fractures in frail elderly resulted in 7 studies that met the eligibility criteria [17–24]; All were nonrandomized, five were retrospective studies. A total of 1189 patients were included, 242 (20.3%) were treated nonoperatively. The mean age ranged from 76.9–101.8 years. The data indicated an unadjusted pooled odds ratio of 3.95-fold and 3.84-fold higher 30-day and 1-year mortality for nonoperative versus operative management. Data also showed that mortality was affected by the number of comorbidities. None of the comparative studies examined (health-related) quality of life, degree of frailty, and costs. The literature review shows a lack of high quality evidence on the true effect of nonoperative versus operative management on quality of life, pain, mortality, complications, and costs in the first 6 months after trauma in frail institutionalized elderly. Those answers are needed to aid patients and health care providers in decision-making for surgical repair, particularly in frail elderly patients. The above shows that the best treatment is not known, and supports the need for high quality evidence. Evidence supporting (non)operative management in terms of quality of life, pain, complications, and mortality is lacking.

It is common practice to decide on treatment following a shared decision process, but still nonoperative treatment is uncommonly used. It is unclear to what extent patients or their relatives currently have a say in the treatment decision.

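### Deaths are called censored in a repeated EQ-5D analysis, so the 6-month non-inferiority contrast describes survivors while the planned conclusion is not limited to them

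*Protocol article*

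**What the plan says.** All of the rule is in the protocol article, section Statistical analysis.

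- Deaths: "Patients who have died will remain in the analysis as censored".
- Missing data, in the next sentence: "If necessary, missing values will be replaced using multiple imputation following the predictive mean matching method, using ten imputations". It does not say whether visits after death count as missing.
- Model: "In the primary GEE model, the primary outcome variable studied (quality of life on EQ-5D) will be analyzed as a dependent variable", with treatment, time and their interaction, corrected for baseline differences and center.
- Test: "This hypothesis will be tested through the adjusted contrast between the two interventions at 6 months".
- Decision: "if the limit of the interval is less than the threshold value of 0.15 points, non-inferiority of nonoperative management to operative management at 6 months" is to be concluded. Nothing limits this to patients alive.

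The Background gives the mortality to be expected: "A 36 and 55% mortality rate within 6 months after fracture has been reported for institutionalized patients and patients with advanced dementia, respectively". It also reports, from non-randomized studies, an "unadjusted pooled odds ratio of 3.95-fold and 3.84-fold higher 30-day and 1-year mortality for nonoperative versus operative management".

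Time to death and mortality at fixed times are separate secondary outcomes (Outcome measures and data collection). QALYs appear only in the economic evaluation.

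**The concern.** Censoring belongs to time-to-event data. It says that an event time is known only to exceed some value. A utility score at a fixed visit has no counterpart: after death there is no later score that follow-up failed to observe. Two readings of the sentence remain.

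1. Visits after death are absent. The GEE still uses a deceased patient's earlier visits, but with a group-by-time term the 6-month contrast is carried essentially by those alive at 6 months.
2. The optional imputation reaches those visits. The deceased then receive utilities borrowed from living patients.

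Death counts against neither arm under either reading. That would matter little if deaths were few or balanced. The protocol's own figures suggest that they may be neither. A claim worded as non-inferiority of the treatment strategy could then rest on a minority of the patients who received it, and the study is meant to inform treatment guidelines.

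**Working it through.** The plan gives no figure for the effect of deaths on the primary contrast, so there is none to reproduce. The check asks how far the answer depends on whether death is counted.

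**Inputs from the protocol article**
- 6-month mortality: 36% (institutionalized patients) and 55% (advanced dementia), Background. Neither is given for an operative arm.
- Odds ratio for death, nonoperative versus operative: 3.95 at 30 days and 3.84 at 1 year, unadjusted, Background.
- Margin 0.15 and SD 0.30, Sample size calculation (0.15 / 0.30 = 0.5 SD, as stated there).
- Utility scale from 0 to 1, Outcome measures and data collection.

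**Assumptions**
- 36% or 55% is taken as operative mortality, or 36% as overall mortality with equal arms.
- The 1-year odds ratio is applied at 6 months.
- Mean utility *u* in survivors is the same in both arms: 0.40, range 0.30 to 0.50.
- Death is scored 0.

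**Formulas**
- Nonoperative odds of death = p_op / (1 - p_op) × OR; p_non = odds / (1 + odds).
- Survivor contrast = u - u = 0.
- Contrast with death = 0: (1 - p_non)·u - (1 - p_op)·u = -(p_non - p_op)·u.

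**Main case:** 0.36 / 0.64 × 3.84 = 2.16; p_non = 2.16 / 3.16 = 0.684. Means with death = 0 are 0.640 × 0.40 = 0.256 and 0.316 × 0.40 = 0.127, a contrast of -0.13.

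| Case | Mortality op / nonop | u = 0.30 | u = 0.40 | u = 0.50 |
|---|---|---|---|---|
| 36% operative, OR 3.84 | 36% / 68% | -0.10 | -0.13 | -0.16 |
| 55% operative, OR 3.84 | 55% / 82% | -0.08 | -0.11 | -0.14 |
| 36% overall, equal arms, OR 3.84 | 21% / 51% | -0.09 | -0.12 | -0.15 |
| 36% operative, OR 2 (assumed) | 36% / 53% | -0.05 | -0.07 | -0.08 |

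The survivor contrast is 0.00 in every row. In the main case the death-inclusive deficit reaches the margin at u = 0.15 / 0.324 = 0.46.

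**Effect on the decision.** A simulation used 80 patients per arm (half of the planned 160), equal survivor means of 0.5, SD 0.30, no loss other than death, no covariate adjustment, and mortality pairs from 21% / 51% to 55% / 82%. The 95% interval met the 0.15 criterion in 37% to 69% of runs with survivors only, and in 1% to 5% with death = 0.

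**Is the survivor contrast itself biased?** This was examined with a latent health score *h* (SD 1, higher is fitter), no true EQ-5D effect, and 36% operative mortality. Mean EQ-5D = 0.4 + 0.3·r·h with r from 0.3 to 0.7. Logit of death = a - b·h, plus log(3.84) in the nonoperative arm, with b from 0.5 to 1.5.
- Arms equal at baseline: crude survivor contrast +0.013 to +0.052, in favor of nonoperative care.
- Nonoperative arm 0.25 SD frailer: about -0.02 to +0.015.
- Nonoperative arm 0.5 SD frailer: -0.009 to -0.069, against nonoperative care.

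These are crude contrasts, before the planned baseline adjustment, and the last two mix confounding with selection. The sign depends on inputs that the document does not give.

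**QALY scale.** Six months is 0.5 year, so a 6-month QALY cannot exceed 0.5. A margin of 0.15 in mean utility corresponds to 0.15 × 0.5 = 0.075 QALY. Testing a QALY difference against 0.15 would allow 0.15 / 0.5 = 0.30 in mean utility.

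**The case against.** **Quality of life while alive is a legitimate target.** The Background faults earlier trials for focusing on mortality, and the Discussion puts comfort and pain first. This stands. It supports a survivor contrast as primary, but the plan does not name that target, and its conclusion is not limited to it.

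**Scoring death as 0 is a value choice.** This stands. A reader might take -0.13 as the error in the planned contrast. It is not: survivors have identical utility in that example, and the whole difference comes from asking another question. It shows only that the two questions can have different answers at the scale of the margin.

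**The mortality contrast may be confounded.** This stands too. A reader might infer that nonoperative care itself raises the odds of death about four-fold. The odds ratios are unadjusted and from non-randomized studies, and the Background says that comorbidity affected mortality. At an odds ratio of 2 the illustration still gives -0.07, about half the margin.

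**Death is reported elsewhere.** Mortality by time point is planned, quality of dying and satisfaction are collected for deceased patients, and QALYs are in the economic evaluation. None of these qualifies the non-inferiority decision.

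**Detail belongs in the full analysis plan.** That would answer silence. Here the article states a rule, and the rule does not fit its own primary model. Whether visits after death would be imputed is open, and a reader should not assume that they would be.

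**Conclusion.** The concern holds in this form. Censoring is undefined for the primary outcome, the 6-month contrast rests essentially on survivors, and the planned conclusion is wider than that contrast supports. Under the stated assumptions, counting death as 0 moves a contrast of 0.00 to between -0.08 and -0.16 when the cited odds ratio is applied, and to -0.07 at an odds ratio of 2 with utility 0.40. The margin is 0.15. The handling of death can therefore decide the conclusion. The size depends on the survivor utility, which the document does not give, and on applying a 1-year unadjusted odds ratio at 6 months.

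A reader might go further and infer that surviving nonoperative patients are a fitter remnant, so that the plan is biased toward non-inferiority. The documents do not support that. The Discussion expects patients who choose nonoperative care to be in worse condition, and the analysis is adjusted for baseline differences. The net direction and size of any selection bias cannot be determined from the document.

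**What to change.** 1. Remove the statement that deaths are censored as far as EQ-5D is concerned. State that values after death are not missing and are not imputed.
2. State that the primary contrast is quality of life among patients alive at 6 months, word the non-inferiority conclusion in those terms, and show mortality by arm beside it.
3. Add a supportive analysis on all enrolled patients: the same adjusted 6-month contrast with EQ-5D = 0 from death onward, its confidence interval compared with 0.15.
4. If the 6-month QALY is also shown, report it with its interval and do not test it against 0.15; the equivalent on that scale is 0.075.
5. If the survivor and death-inclusive results disagree, do not claim unqualified non-inferiority.

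The cost is a change of wording and one extra model on data already collected. An unqualified claim becomes harder to make if mortality differs between the arms.
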